### 2.2. Sample Size Calculation

The primary analysis (see below) will focus on total severity of APS as evaluated using the Comprehensive Assessment of At-Risk Mental State (CAARMS) [1], measured in three longitudinal assessments (i.e., Feasibility phase: Baseline, T1, and T2). Accepting a type-I error (α) of 5% and a type-II error (β) of 20%, we would need a sample of 8–12 participants to detect an effect of large size (partial-η2 ≥ 0.140). This value was obtained considering a moderate-to-large test-retest reliability of measurements over time (+0.500 < r ≤ +0.700) and the absence of correction for sphericity. With an intermediate sphericity correction (ε = 0.750), the required sample size would be 10–14; in the worst case (ε = 0.500), instead, 12–19 participants would be needed. We therefore propose the recruitment of 20 participants, considered coherent with a pilot study and sufficient to evaluate feasibility outcomes of clinically significant size, also considering a low drop-out rate (i.e., ≤ 20%). When large statistically significant results are obtained on total severity of APS, specific APS severities will be further investigated (i.e., considering four P1 scales). For this secondary endpoint, on average, a sample-size of 17 participants would be sufficient to detect large effects, also considering Bonferroni’s correction for multiple independent comparisons (i.e., α = 0.012). Power analyses were carried out with G*Power-3.1.9.7 [45].

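### Naming Holm's step-down for the four P1 scales would keep the same 5% familywise error as Bonferroni and gain 0 to about 10 points of power per affected scale

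*Protocol article*

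**What the plan says.** The relevant text is in section 2.2 (Sample Size Calculation) of the protocol article. If total APS severity gives a large significant result, "specific APS severities will be further investigated (i.e., considering four P1 scales"). For this secondary family the article states that "on average, a sample-size of 17 participants would be sufficient to detect large effects", "also considering Bonferroni’s correction for multiple independent comparisons (i.e., α = 0.012").

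The primary calculation in the same section supplies the other inputs: "to detect an effect of large size (partial-η2 ≥ 0.140"), "measured in three longitudinal assessments (i.e., Feasibility phase: Baseline, T1, and T2"), and "moderate-to-large test-retest reliability of measurements over time (+0.500 < r ≤ +0.700"). Twenty participants are to be recruited, with drop-out of at most 20%.

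Section 2.8.1 (Data Verification, Statistical Monitoring, and Analysis) names no multiplicity procedure. It leaves details to a Statistical Analysis Plan to be approved before any data are summarised. Bonferroni, in the sample-size section, is therefore the only correction the article names for these four scales.

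**The concern.** Bonferroni compares every one of the four p-values with 0.05/4. Holm orders them and compares the smallest with 0.05/4, the next with 0.05/3, then 0.05/2, then 0.05, stopping at the first that fails. Both hold the familywise error at 5% whatever the dependence between scales, and Holm rejects everything that Bonferroni rejects. Neither method needs the independence that the article's wording suggests.

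The scales are examined only once their total is significant, so more than one true effect is plausible, though not assured. That is the situation in which a step-down helps. The sample may be as small as 16 completers. What is at stake is some power in a secondary analysis; validity is not affected.

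**Working it through.** **Inputs from section 2.2.** Partial η² = 0.14, so f² = 0.14/0.86 = 0.1628. There are m = 3 visits and one group. The correlation between visits r runs from 0.5 (itself excluded) to 0.7. Sphericity ε is 1, 0.75 or 0.5. The family has four scales. Completers: 20 − 20% of 20 = 16.

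**Input assumed.** The article gives no correlation between the scales. I take 0.3 and vary it from 0 to 0.6.

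**Step 1: reproduce the plan's figures.** For a one-group repeated-measures F test, λ = f²·n·m·ε/(1 − r), df1 = (m − 1)ε and df2 = (n − 1)(m − 1)ε.

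- At α = 0.05 and 80% power, the required n is 8–12 (ε = 1), 10–14 (ε = 0.75) and 12–19 (ε = 0.5). These are exactly the stated ranges.
- At α = 0.0125 the required n is 11–16, 13–20 and 17–27. The mean of these six values is 104/6 = 17.3, and the middle case (r = 0.6, ε = 0.75) gives 17. The stated average of 17 is confirmed.
- 0.05/4 = 0.0125, and the printed 0.012 is that value cut to three decimals (4 × 0.012 = 0.048). This changes n by at most 1.

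**Step 2: Holm's thresholds.** 0.05/4 = 0.0125, 0.05/3 = 0.0167, 0.05/2 = 0.025, 0.05/1 = 0.05.

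**Step 3: why the gain depends on the number of affected scales.** At n = 16, r = 0.5 and ε = 1, λ = 0.1628 × 16 × 3/0.5 = 15.6 with 2 and 30 degrees of freedom. Power of a single scale is then 80.5% at 0.0125, 83.6% at 0.0167, 87.6% at 0.025 and 93.0% at 0.05. Leaving aside a chance false rejection of an unaffected scale, with k affected scales the loosest threshold any of them can reach is 0.05/(5 − k). One affected scale therefore stays at 0.0125 and gains nothing. Only with four can the last be tested at 0.05.

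**Step 4: simulation.** Settings: n = 16, ε = 1, between-scale correlation 0.3, large effect on each affected scale. The table gives average power per affected scale. The simulation does not condition on a significant total.

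| r | Bonferroni | Holm, 1 affected | Holm, 2 affected | Holm, 3 affected | Holm, 4 affected |
|---|---|---|---|---|---|
| 0.5 | 80% | 80% | 83% | 86% | 90% |
| 0.6 | 90% | 90% | 92% | 94% | 96% |
| 0.7 | 97% | 97% | 98% | 98–99% | 99% |

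Further results, all with four affected scales:

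- Power to detect all four at n = 16 rises from 48% to about 75% at r = 0.5, and from 89% to 98% at r = 0.7.
- With between-scale correlation from 0 to 0.6 (n = 16, r = 0.5), Holm's per-scale power is 91% to 89%. Power for all four is 73% to 80%, against 41% to 58% under Bonferroni.
- At n = 20 and r = 0.5, per-scale power rises from 91% to 96–97%, and power for all four from 72% to 90%.
- With half of f and r = 0.6, per-scale power rises from 23–24% to 28–29% (n = 16) and from 33% to 40% (n = 20).

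Using 0.012 in place of 0.0125 costs Bonferroni only about half a point per scale (80.1% against 80.5%). The gain therefore comes from the step-down and not from the rounding.

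**Step 5: error control.** In simulations with between-scale correlation 0 or 0.5 and at least one unaffected scale, Holm's familywise error was 0.036 to 0.051, consistent with 0.05 within simulation error.

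**The case against.** The strongest reply is that Bonferroni appears only in a sample-size sentence. Sizing at a quarter of the overall level is also a sound conservative basis for a trial later analysed by Holm, whose first threshold is the same 0.0125. The unseen SAP may well name a step-down. This stands in part. A reader might infer that the plan commits to testing all four scales at a fixed 0.012, but the text does not go that far. Bonferroni is still the only correction named, so it would be the natural default unless something else is written down.

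A second reply is that the largest figures describe the most favourable case: four large effects, r at the excluded lower end of the stated range, and no sphericity correction. This stands. A significant total can be driven by one or two scales. The Introduction also reports that earlier PEA studies did not significantly improve positive psychotic symptoms, so four large effects are not the natural expectation. Detecting all four scales is not a goal the plan sets, and the rise from 48% to about 75% should be read with that in mind.

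A third reply is that little depends on this. The family is secondary and examined only after a significant total, in an open-label, single-arm feasibility pilot. That also stands and limits the weight of the point.

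**Conclusion.** The point holds as a small efficiency improvement. At 16 completers, with the plan's large effect, ε = 1 and an assumed between-scale correlation of 0.3, Holm adds between 0 and about 10 percentage points of average power per affected scale. At r = 0.5 the gain is nil with one affected scale, about 2–3 points with two, 5–6 with three and 9–10 with four. With four affected it is about 6 points at r = 0.6 and about 2 at r = 0.7. It is never negative.

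Two stronger readings are not supported. A reader might infer that the multiplicity correction or the figure of 17 is wrong, but Bonferroni controls the familywise error and 17 reproduces. A reader might also infer that a step-down was weighed and rejected, but the article nowhere mentions one.

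**What to change.** Add one sentence to the statistical methods or the SAP: after a significant result on total APS severity, the four P1 scales will be tested with Holm's step-down procedure at familywise α = 0.05. Keep 17 in section 2.2 and describe it as a conservative planning figure based on Bonferroni.

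The sentence should be in place before any data are summarised. The only cost is that simultaneous confidence intervals are less simple than under Bonferroni, and the article does not rely on such intervals. The primary test, the recruitment of 20 and the feasibility criteria stay as they are.

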### 2.3. Objectives

#### 2.3.1. Feasibility Endpoints

We will record (i) the number of subjects giving consent for participating to the trial; (ii) the proportion of participants completing the initial 12-week follow-up. Patients will be defined as compliant in the presence of a pill count greater than 50% the expected number taken. Patients who are defined as non-compliant with the medication will be coded as protocol deviators.

#### 2.3.2. Research Endpoints

We will primarily address whether um-PEA added to treatment as usual (TAU) in CHR patients improves APS. Our secondary research questions are whether um-PEA added to TAU in CHR patients improves APS to the extent that patients no longer satisfy the diagnostic criteria for the CHR state, relieves APS-associated distress, improves CHR-related anxiety symptoms, and ameliorates social and role functioning, as well as general psychopathology and wellbeing measures. Therefore, our primary endpoint will be the assessment of APS severity as measured using the CAARMS [1]. As per the secondary endpoints: (i) APS-associated distress will be measured using the CAARMS [1]; (ii) severity of CHR-related anxiety symptoms will be measured using the Hospital Anxiety and Depression Scale (HADS) [43]; (iii) the level of impaired global functioning will be measured using the Social and Role functioning Scale [44]; (iv) clinical remission, defined as no longer meeting the APS criteria [1] will be measured using the CAARMS [1]; (v) general psychopathology and wellbeing changes will be measured using the CAARMS [1].

All the study endpoints for the 12-week clinical trial will be assessed by comparing follow-up (FUP) visits and baseline. For those participants continuing in the 24-week extension phase, change (FUP visit minus baseline) in the severity of psychotic symptoms as measured using the CAARMS will be compared with the group of those willing to discontinue um-PEA and continue with TAU. Should the psychopathological condition require TAU adjustments based on clinical judgement, this will be mentioned in a specific section of the trial case report form (CRF; https://osf.io/2vayh, accessed on 5 December 2024).

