#### 2.5.2. Inclusion Criteria

The following are the participants’ inclusion criteria:Individuals diagnosed with CHR-APS, as defined using CAARMS criteria [1];Aged 18–35 years;To be able to understand and communicate in Italian;To be able to give informed consent.

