### 2.8. Statistical Methods

#### 2.8.1. Data Verification, Statistical Monitoring, and Analysis

At the study start, a structured data verification plan will be agreed and developed by the Head Statistician ([name]) of the research team. Quality of data will be routinely checked in terms of consistency across paper- and electronic-based entry systems. Statistical monitoring will include patient severity level, eventual withdrawals, baseline data, FUP visits data, and adverse effects. The research team will approve a Statistical Analysis Plan within the early stages of the study, and before the Head Statistician summarizes any data (i.e., with univariate and repeated measures analysis, including preliminary assessment and management of any outliers and assessment of the metric qualities of measurements, such as normality and sphericity, where necessary). Proportions will be presented for each feasibility outcome. Interim analyses are not planned. The Head Statistician will both carry out and interpret statistical analysis. Our primary analysis will involve a generalized linear model with CAARMS psychotic symptom severity as the dependent measure and time as a repeated measure (possibly supplemented with analyses at the participant level, as random effects in mixed models). We are interested in whether there is a significant benefit over time with um-PEA treatment: therefore, particular interest will be placed on time as a fixed factor on the severity of outcomes. CAARMS distress and total score as well as HADS and GF ratings will be analysed in a similar manner. We will also conduct paired tests (both parametric and non-parametric) based on baseline and endpoint assessments to examine measures of CAARMS severity, CAARMS frequency/duration, and secondary outcomes. Trend and rates of adverse effects will be reported, as well as reasons for dropouts from the trial.

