### 2.9. Withdrawal of Participants

In accordance with the Declaration of Helsinki [55], all participants have the right to withdraw from the study at any time, without the need to provide a reason, and without affecting their future medical care. Participants will be informed of this right prior to giving consent. If a participant decides to withdraw, it will be clarified that they are only discontinuing the study treatment while continuing follow-up visits. Should a participant wish to fully withdraw from the study, their decision will be respected. Efforts will be made to determine the reason for withdrawal, although participants are not required to provide any explanation. Data already collected will be retained and included in the final analysis. The PI may also withdraw participants for various reasons, including but not limited to protocol violations, intercurrent illness, adverse events, serious adverse events, suspected unexpected serious adverse reactions, administrative reasons, or if participation in the trial interferes with ongoing care or results in symptomatic worsening.

In these cases, participants will continue to be followed up with the same schedule of research assessments as those who remain in the study, until they complete the 12-week follow-up period or until they develop frank psychosis, whichever occurs first. Participants who experience progression to first-episode psychosis will exit the study intervention, be classified as treatment failure, and only be assessed for safety outcomes until completing the 12-week follow-up period.

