## Figures and Tables

**Table 1 brainsci-14-01230-t001:** Study flowchart.

Procedures	Screening Phase	Feasibility Phase			Extension Phase	
	Screening (Day-7)	Baseline (Day 0)	T1 (4 weeks ± 7 Days)	T2 (12 Weeks ± 14 Days)	T3 (24 Weeks ± 14 Days)	T4 (36 Weeks ± 14 Days)
Informed consent	X					
Medical history	X					
Physical examination	X	X		X		X
Electrocardiogram	X	X		X		X
Urinalysis	X			X		X
*AUDIT* [37], *FTND* [38], *SDS* [39], *CEQ* [40]	X					
*TFLB* [41]		X	X	X	X	
Pregnancy test	X	X	X	X	X	
Hematology, biochemistry	X			X		X
Concomitant medication	X	X	X	X	X	X
Exclusion criteria	X	X				
Intelligence quotient	X					
*UKU-SERS* [42]		X	X	X	X	X
*Um-PEA* dispensing		X	X	X	X	
Compliance assessment			X	X	X	X
*CAARMS* [1]	X	X	X	X	X	X
*HADS* [43], *GF* Social/Role scales [44]		X	X	X	X	X
Microbiome, inflammation, eCBome blood and stool assessments		X	X	X	X	X

*AUDIT*, Alcohol Use Disorders Identification Test; *FTND*, The Fagerstorm Test for Nicotine Dependence; *SDS*, Severity of Dependence Scale; *CEQ*, Cannabis Experience Questionnaire; *TFLB*, The Timeline Followback; *UKU-SERS*, UKU Side Effect Rating Scale; *Um-PEA*, Ultramicronized-Palmitoylethanolamide; *CAARMS*, The Comprehensive Assessment of At-Risk Mental State; *HADS*, Hospital Anxiety and Depression Scale; *GF*, Global Functioning.

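### Clinical remission is to be compared with a baseline at which it is 0% by eligibility, so a paired test asks only whether anyone remits; its definition is also broader than the research question

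*Protocol article*

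**What the plan says.** All references are to the protocol article.

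- **Endpoint.** Section 2.3.2, secondary endpoint (iv): "clinical remission, defined as no longer meeting the APS criteria [1] will be measured using the CAARMS".
- **Research question behind it.** The same section asks whether um-PEA added to usual treatment "improves APS to the extent that patients no longer satisfy the diagnostic criteria for the CHR state".
- **Comparison rule.** Section 2.3.2 again: "All the study endpoints for the 12-week clinical trial will be assessed by comparing follow-up (FUP) visits and baseline". No endpoint is exempted.
- **Tests.** Section 2.8.1: "We will also conduct paired tests (both parametric and non-parametric) based on baseline and endpoint assessments". That sentence goes on to name secondary outcomes among the measures covered.
- **Entry.** Section 2.5.2: "Individuals diagnosed with CHR-APS, as defined using CAARMS criteria".
- **Transition to psychosis.** Section 2.9 says that participants who progress will leave the intervention, "be classified as treatment failure", and have only safety outcomes assessed for the rest of the 12 weeks.
- **Missing data.** Section 2.8.2 includes anyone with at least one post-baseline measure and allows multiple imputation or MissForest.

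The trial is single-arm (section 2.1), and no benchmark remission rate is stated.

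**The concern.** A rule that suits severity scores has been extended to an endpoint it does not suit. A severity score can rise or fall from baseline, so no change on average is a meaningful null hypothesis. Remission cannot behave that way. Everyone enters unremitted, so the only possible change is towards remission, and the null hypothesis of a paired test holds only if nobody ever remits. Rejecting it says nothing about um-PEA.

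Section 3 presents this trial as the justification for a larger Phase-3 study. A significant remission result obtained against a baseline fixed at zero could be carried into that planning as a sign of benefit.

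Two smaller matters concern the numerator and denominator. The endpoint asks about leaving the APS group, the research question about leaving the CHR state, and section 3 names two other CHR groups (vulnerability and BLIPS). Also, section 2.9 labels a transition as failure without saying how that person enters the remission proportion.

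**Working it through.** **The plan's own figures.** The article gives no number for remission. Its sample sizes concern the primary repeated-measures analysis. They reproduce with λ = N·m·f²·ε/(1−r), df1 = (m−1)ε, df2 = (N−1)(m−1)ε, m = 3, f² = 0.14/0.86, α = 0.05 and power 80%. For r = 0.7 and 0.5, N is 8 and 12 at ε = 1, 10 and 14 at ε = 0.75, and 12 and 19 at ε = 0.5, as section 2.2 states. None of this depends on remission.

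**Paired test against a structural zero.** Let k participants go from not remitted to remitted. Nobody can go the other way, because nobody is remitted at entry. The two-sided exact McNemar p-value is then 2 × 0.5^k:

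- k = 5: 2 × 1/32 = 0.0625
- k = 6: 2 × 1/64 = 0.031

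The threshold is six remitters whether 20 participants are analysed (30%) or 16 (37.5%). Sixteen is 80% of 20, the completion target in section 2.1.

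**How often an inert treatment would pass.** This is P(X ≥ 6) for a binomial count. The spontaneous 12-week remission rate is assumed, since the article gives none.

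| Assumed spontaneous remission | N = 20 | N = 16 |
|---|---|---|
| 10% | 1.1% | 0.3% |
| 20% | 19.6% | 8.2% |
| 30% | 58.4% | 34.0% |
| 40% | 87.4% | 67.1% |
| 50% | 97.9% | 89.5% |

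**What a descriptive report would give.** Exact (Clopper-Pearson) 95% intervals: 6/20 = 30%, 11.9% to 54.3%; 10/20 = 50%, 27.2% to 72.8%; 6/16 = 37.5%, 15.2% to 64.6%.

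**Treatment failures in the denominator.** Section 1 gives a two-year transition risk of 16–19%. Under an assumed constant hazard, the 12-week risk is 1 − (1 − q)^(12/104), which is 0.0199 for q = 0.16 and 0.0240 for q = 0.19. Among 20 participants that is 0.40 to 0.48 expected transitions, with a 33.1% to 38.5% chance of at least one.

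Such a person may have no T2 CAARMS, because section 2.9 limits further assessment to safety. With six remitters and one transition, the result is:

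- 6/20 = 30.0% if the person is kept as not remitted
- 6/19 = 31.6% if excluded
- 7/20 = 35.0% if imputed as remitted

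**Definition against question.** The endpoint is met by leaving the APS group. The question requires that participants "no longer satisfy the diagnostic criteria for the CHR state". Someone who left the APS group but met criteria for another CHR group would satisfy the first and not the second.

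**The case against.** The strongest reply is that no test is named for remission. Comparing with baseline could simply be how remission is ascertained, and parametric and non-parametric paired tests fit scale scores most naturally. An analysis plan that is not shown may settle the detail. It is true that McNemar is inferred. But the article itself sets a comparison rule for all endpoints and extends paired tests to secondary outcomes without exempting remission. Any paired test against a fixed 0% has the same defect.

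A second reply is that this is only the single-arm limitation, which section 3 acknowledges by calling for randomization and blinding in future studies. That limitation does apply to every endpoint. Remission has a further problem, because its null hypothesis is false as soon as one person could remit.

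A third reply is that movement to another CHR group depends on CAARMS rules in a cited source that is not shown. That stands, so its frequency cannot be judged. The mismatch in wording remains.

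Three stronger readings are tempting, and the documents do not support them:

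- A reader might infer that a transition to psychosis counts as remission, since a person with psychosis may no longer meet APS criteria. Section 2.9 makes it a treatment failure with safety-only follow-up, and the research question requires improvement. What is missing is only a link between that rule and the remission denominator.
- A reader might infer that the whole remission result is uninterpretable. The proportion is a sound description in a pilot; only the test against baseline is uninformative.
- A reader might infer that someone already below the APS threshold at Day 0 would be counted as a remitter. Table 1 schedules a CAARMS at Day 0, so the case would be visible. If still below threshold at T2, that person would show no change in a paired comparison.

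**Conclusion.** The point holds, and it is minor. As written, sections 2.3.2 and 2.8.1 put clinical remission under a comparison with a baseline that eligibility fixes at 0%. A paired test would be significant from six remitters onward and could not separate an effect of um-PEA from natural remission. At 20 participants, an inert treatment would pass in about 20% to 87% of trials over an assumed spontaneous remission range of 20% to 40%. Those percentages rest on that assumed range and on the exact McNemar test; the defect itself needs neither.

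The endpoint definition is broader than its research question. The handling of treatment failures is incomplete, at a cost of a few percentage points in a proportion whose interval is tens of points wide. Neither the primary analysis nor the sample size is affected.

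**What to change.** Four changes of wording:

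1. In sections 2.3.2 and 2.8.1, exempt clinical remission from the comparison with baseline and from the paired tests.
2. State that remission will be reported as the proportion remitted at T2 with an exact 95% confidence interval.
3. Align the endpoint definition with the research question on the CHR state, so that both describe the same outcome.
4. Cross-refer to section 2.9: participants classified as treatment failure stay in the denominator as not remitted, and are neither excluded nor imputed under section 2.8.2.

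The cost is a few sentences and no new data, since CAARMS is already scheduled at baseline and T2. The downside is a slightly lower reported remission rate and no p-value for this endpoint.

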## 2. Materials and Methods

### 2.1. Trial Design

This is a 12-week, open-label, investigator-initiated, proof-of-concept, single-arm study (Phase-2 Pilot Study) assessing the effect of um-PEA 600 mg/day in CHR individuals presenting with APS [1]. Within the first 12 months from the first participant recruitment, we will assess the feasibility of enrolling a minimum of 20 CHR participants and whether at least 80% of participants have completed the 12-week follow-up. After completing the initial 12-week phase, participants will be proposed to enter a 24-week extension phase of the study to evaluate the clinical stability of the treatment. Based on clinical judgement of the improvement obtained at that point, um-PEA might be titrated to 1200 mg/day. Each participant will undergo um-PEA treatment for a maximum of 36 weeks (Table 1). Our purpose is to examine: (i) um-PEA ability to alleviate APS and anxiety symptoms in CHR patients; (ii) um-PEA safety and tolerability; (iii) the biological basis of um-PEA effect. The study was approved by the Department of Medicine (DMED) at University of Udine (Institutional Review Board: 93/2023) in June 2023 (https://osf.io/wn2kf, accessed on 5 December 2024).

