### 2.6. Intervention

Participants will initially undertake a 12-week daily treatment with oral um-PEA 600 mg in tablet form (Normast^®^). During the 24-week extension phase of the study, the trial medication will be taken from once a day up to twice a day (600–1200 mg per day), based on clinical judgment of the improvement obtained at that point, around mealtime. Being a food supplement/nutraceutical, um-PEA can be purchased at pharmacies without a medical prescription [52]. While unknown risks cannot be excluded, serious adverse events including overdose have not been documented [53,54]. Um-PEA will be obtained by a pharmaceutical company operating under good manufacturing practice conditions with appropriate certification.

The information presented on the labels for um-PEA will comply with applicable national and local regulations. Only qualified physicians clearly given this role by the PI will prescribe the study medication on the study delegation log. Only people designated by the PI will collect medication. Only um-PEA supplied for this study will be dispensed against the study specific prescription. Full accountability records will be completed including recording the batch, expiry date, people dispensing/checking the prescription, quantity and date of drug returns, empty packaging. Nothing will be destroyed without the authorization from the PI.

Um-PEA will be stored at room temperature (<25 °C) and not kept in a refrigerator, in compliance with local regulations. It will be stored in a secure area away from other treatments and clearly marked for this study.

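### The extension comparison measures change from Day 0 between self-chosen groups, so any difference in their 12-week response is counted as a difference between continuing and stopping um-PEA

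*Protocol article*

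**What the plan says.** Section 2.3.2 (Research Endpoints) sets the outcome for participants who enter the extension as "change (FUP visit minus baseline) in the severity of psychotic symptoms as measured using the CAARMS", and this "will be compared with the group of those willing to discontinue um-PEA and continue with TAU".

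Three other places fix how that reads:

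- **Reference visit.** Table 1 gives the name Baseline to Day 0 only. Week 12 is T2, and no separate baseline is defined for the extension. The sentence just before the comparison uses the same word for the 12-week endpoints.
- **Common treatment before the choice.** Section 2.6: "Participants will initially undertake a 12-week daily treatment with oral um-PEA 600 mg in tablet form".
- **Timing of the choice.** Section 2.1 offers the extension only once the 12-week phase is complete, and gives its aim as judging how stable the clinical result is. The study is single-arm and open-label, so participants decide after 12 weeks on a treatment they know they are taking.

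Neither section 2.3.2 nor section 2.8.1 adjusts this comparison for the T2 score or the 12-week response. The Discussion says that later studies will need randomisation and blinding, but does not discuss this contrast.

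**The concern.** The groups form at week 12, but the outcome clock starts at Day 0. The first 12 weeks of the measured change therefore predate the choice, and both groups were assigned the same treatment then. If those who improved more are more inclined to stay on, they enter the extension already ahead and that lead is credited to continuing. If those who have remitted feel they can stop, the error runs the other way.

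This is the only between-group comparison the article describes, in a trial that the Discussion presents as grounds for a Phase-3 study. As specified, it cannot separate what happens after continuing or stopping from what had already happened. The article states the outcome, the reference visit and the comparator, so this is a stated rule that works badly and not a detail left to the analysis plan.

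**Working it through.** **The plan's own figures.** Section 2.2 gives sample sizes for the time effect over three visits and none for the extension comparison. They reproduce with a noncentral F test with f² = 0.14/0.86 = 0.163, m = 3, λ = f²·n·m·ε/(1 − r), and degrees of freedom (m − 1)ε and (n − 1)(m − 1)ε. For example, n = 12, r = 0.5, ε = 1 gives λ = 0.163 × 12 × 3/0.5 = 11.7 and power 0.82. The required n at r = 0.5 and r = 0.7 is 12 and 8 (ε = 1), 14 and 10 (ε = 0.75), 19 and 12 (ε = 0.50), as stated. These concern the 12-week analysis only.

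**Decomposition.** T4 − Day 0 = (T2 − Day 0) + (T4 − T2). The first term predates the choice. A part of it equal in both groups cancels; a part that differs does not.

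**Inputs.** From section 2.2: correlations r of 0.5 to 0.7, N = 20, and drop-out up to 20%, so 20 × 0.8 = 16 completers. Assumed, because the article does not give them: those correlations hold equally among Day 0, T2 and T4; each score has SD 1; 60% continue; a correlation b links 12-week improvement to the underlying willingness to continue. The true effect of continuing is set to zero.

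**Formula.**

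- SD of (T2 − Day 0) = √(2(1 − r)): 1.000 at r = 0.5 and 0.775 at r = 0.7.
- Slope of (T4 − Day 0) on (T2 − Day 0) = (1 − r)/(2(1 − r)) = 0.5.
- If a fraction p continues, the standardised gap in willingness between the groups is k = φ(z)/(p(1 − p)): 1.596 at p = 0.5, 1.610 at p = 0.6, 1.656 at p = 0.7.
- Spurious difference = k × b × 0.5 × SD of (T2 − Day 0).

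| Dependence of choice on response | r = 0.5 | r = 0.7 |
|---|---|---|
| b = 0 | 0 | 0 |
| b = 0.3, p = 0.6 | 1.610 × 0.3 × 0.5 × 1.000 = 0.24 | 1.610 × 0.3 × 0.5 × 0.775 = 0.19 |
| b = 0.5, p = 0.6 | 0.40 | 0.31 |
| b = 0.7, p = 0.6 | 0.56 | 0.44 |
| response alone decides (b = 1), p = 0.5 | 1.596 × 0.5 × 1.000 = 0.80 | 1.596 × 0.5 × 0.775 = 0.62 |
| response alone decides (b = 1), p = 0.7 | 0.83 | 0.64 |

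Simulation agrees to within about 0.01. The values favour continuing when improvers stay on; reversing the sign of b mirrors them. With 16 completers and a two-sided 5% t-test, the simulated false-positive rate is about 5% at b = 0 and about 7%, 11% and 18 to 19% at b = 0.3, 0.5 and 0.7.

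**If gains persist fully.** This is a further assumption (SD of the 12-week change 1, SD of later change 0.5). The slope becomes 1 in place of 0.5, giving 1.610 × b = 0.48, 0.81 and 1.13 at b = 0.3, 0.5 and 0.7, with false-positive rates of 12%, 28% and 53%.

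**Change from T2 instead.** Under equal correlations the slope of (T4 − T2) on (T2 − Day 0) is −0.5, so the error has the same size and the opposite sign: simulated +0.19 to +0.57 SD for b = 0.3 to 0.7. It is zero only if gains persist fully.

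**T4 regressed on group, Day 0 and T2.** The simulated group coefficient is 0.00, within 0.01, throughout the equal-correlation model.

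**Precision.** With 16 completers split 10:6, normal-approximation power is 34% for a difference of 0.8 SD and 49% for 1.0 SD.

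**The case against.** The strongest reply is that nothing in the article says response drives the choice. Section 2.3.2 speaks only of willingness, and improvement is mentioned as a guide to dose, not to entry into the extension. That stands. A reader might infer that the comparison will show a large difference in favour of continuing; the documents do not support this, because both size and sign depend on an unstated mechanism. The 0.6 to 0.8 SD figures are the extreme case in which response alone decides.

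A reader might also infer that those who stop have no scheduled outcome data, since section 2.9 follows people "until they complete the 12-week follow-up period or until they develop frank psychosis, whichever occurs first". That rule concerns withdrawal from the study, not people who complete week 12 and decline the extension, and the planned comparison presupposes that their data exist. What remains is narrower: Table 1 lists T3 and T4 only under the extension phase, so whether decliners attend is not stated in the article.

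Section 2.1 adds: "Based on clinical judgement of the improvement obtained at that point, um-PEA might be titrated to 1200 mg/day". It is tempting to extend the point to a dose comparison, but none is planned.

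The zero from covariate adjustment is partly built in, because the simulated choice depends only on the measured scores and independent noise. Selection on tolerability, distress or changes in usual treatment would remain.

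Finally, the article is open about being single-arm and proof-of-concept, gives clinical stability as the aim of the extension, and does not number this comparison among its secondary endpoints. It would be speculation to say that it will be read as controlled evidence. These facts lower the weight of the point but do not repair the contrast.

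**Conclusion.** The point holds in a bounded form. As specified, the extension contrast includes a period before the groups existed, so any group difference in 12-week response is counted as a difference between continuing and stopping. With no true effect and equal correlations of 0.5 to 0.7, the spurious difference runs from 0, through about 0.2 to 0.6 SD for b between 0.3 and 0.7, to about 0.6 to 0.8 SD when response alone decides. It can run in either direction. The correlation range comes from section 2.2; its extension to T4, the proportion continuing and the strength of selection are assumptions.

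This is a should-fix. The feasibility endpoints, the 12-week primary analysis and its sample size are unaffected.

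**What to change.** - Replace the change-from-Day-0 comparison by T3 and T4 CAARMS severity regressed on group as chosen at T2, with Day 0 and T2 CAARMS as covariates. Keep each participant in the group chosen at T2. Do not simply substitute change from T2.
- Report the estimate and confidence interval as descriptive and non-randomised, and note that selection on unmeasured factors remains.
- State whether week-12 completers who decline the extension have T3 and T4 CAARMS ratings. If they do not, delete the comparison. This should be settled before participants reach week 12, since missed ratings cannot be recovered.

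The cost is a change of wording, two covariates and, if they are not already planned, T3 and T4 ratings for those who stop. The price to accept is an estimate that may well be wider, since group and T2 score are correlated when response drives the choice and there are only about 16 completers. It would probably also be less favourable to continuing, if responders are the ones who stay on. Treatment is unchanged.
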